# Study protocol of a randomised controlled trial comparing perioperative intravenous insulin, GIK or GLP-1 treatment in diabetes–PILGRIM trial

**DOI:** 10.1186/1471-2253-14-91

**Published:** 2014-10-14

**Keywords:** Diabetes mellitus type 2, Perioperative management, GLP-1 agonist

## Abstract

**Background:**

Diabetes mellitus (DM) is associated with poor outcome after surgery. The prevalence of DM in hospitalised patients is up to 40%, meaning that the anaesthesiologist will encounter a patient with DM in the operating room on a daily basis. Despite an abundance of published glucose lowering protocols and the known negative outcomes associated with perioperative hyperglycaemia in DM, there is no evidence regarding the optimal intraoperative glucose lowering treatment. In addition, protocol adherence is usually low and protocol targets are not simply met.

Recently, incretins have been introduced to lower blood glucose. The main hormone of the incretin system is glucagon-like peptide–1 (GLP-1). GLP-1 increases insulin and decreases glucagon secretion in a glucose-dependent manner, resulting in glucose lowering action with a low incidence of hypoglycaemia.

We set out to determine the optimal intraoperative treatment algorithm to lower glucose in patients with DM type 2 undergoing non-cardiac surgery, comparing intraoperative glucose-insulin-potassium infusion (GIK), insulin bolus regimen (BR) and GPL-1 (liragludite, LG) treatment.

**Methods/Design:**

This is a multicentre randomised open label trial in patients with DM type 2 undergoing non-cardiac surgery. Patients are randomly assigned to one of three study arms; intraoperative glucose-insulin-potassium infusion (GIK), intraoperative sliding-scale insulin boluses (BR) or GPL-1 pre-treatment with liraglutide (LG). Capillary glucose will be measured every hour. If necessary, in all study arms glucose will be adjusted with an intravenous bolus of insulin. Researchers, care givers and patients will not be blinded for the assigned treatment. The main outcome measure is the difference in median glucose between the three study arms at 1 hour postoperatively. We will include 315 patients, which gives us a 90% power to detect a 1 mmol l^−1^ difference in glucose between the study arms.

**Discussion:**

The PILGRIM trial started in January 2014 and will provide relevant information on the perioperative use of GLP-1 agonists and the optimal intraoperative treatment algorithm in patients with diabetes mellitus type 2.

**Trial registration:**

ClinicalTrials.gov, NCT02036372

## Background

It is expected that the worldwide prevalence of diabetes will increase from 220 million people now, to 300 million people in 2025 [1]. Type 2 diabetes mellitus (DM) is most common and accounts for 80% of the diabetic cases in the Western World [2]. Because DM is accompanied by macro- and microvascular complications, people with DM are more likely to be admitted to the hospital than people without DM. Twenty-two percent of in-hospital days are occupied by patients with DM, who are especially over-represented in the surgical population [3–5]. The prevalence of DM in hospitalised patients is up to 40% [3], thus the anaesthesiologist will encounter a patient with DM in the operating room on a daily basis.

Patients with DM have an increased risk of developing hyperglycaemia during and after surgery. The glycaemic control in the first 24 hours after surgery in patients with DM is poor and associated with an increased risk of postoperative infections [6–8]. In addition, hyperglycaemia is associated with increased risk of postoperative complications and length of hospital stay, irrespective of the diagnosis of DM [9–13].

Considering the high prevalence of DM in the operating theatre, the lack of evidence with regard to perioperative glucose regulation in non-cardiac surgery patients with DM is surprising. In contrast, stress hyperglycaemia in the ICU or in cardiac surgery patients has been investigated in a vast number of trials [14–16], but these studies did not focus on DM [17].

For the perioperative glucose regulation multiple protocols have been developed, ranging from intravenous glucose-insulin-potassium infusion to subcutaneous sliding-scale insulin bolus regimens. Despite this abundance of published glucose lowering protocols and the proven negative associations of perioperative hyperglycaemia in DM, there is no evidence to support an optimal perioperative glucose lowering treatment. In addition, DM protocol adherence is surprisingly low and glucose targets are frequently not achieved [18]. Considering only the postoperative period, the reduction of 1 mmol l^−1^ glucose in the RABBIT 2 surgery trial with a subcutaneous basal-bolus regimen compared to sliding scale algorithm significantly reduced postoperative complications in patients with DM type 2 [19]. These data also suggest that we cannot simply tolerate glucose levels above 10 mmol l^−1^.

Recently, incretins have been introduced to lower blood glucose. The main hormone of the incretin system is glucagon-like peptide–1 (GLP-1). GLP-1 increases insulin and decreases glucagon secretion in a glucose-dependent manner, resulting in low incidence of hypoglycaemia, which is a major advantage in the perioperative period and may reduce workload, thereby improving compliance. Intravenous administration of GLP-1 after major abdominal surgery normalised blood glucose levels, without causing hypoglycaemic events [20].

In conclusion, DM is a relevant and prevalent disease, which predisposes surgical patients to hyperglycaemia and postoperative complications. Despite being one of the most encountered co-morbidities in the operating theatre, there is a lack of clinical trials regarding the optimal perioperative management of elevated glucose levels. Our primary objective is to investigate the optimal intraoperative treatment algorithm to lower glucose in patients with DM type 2 undergoing non-cardiac surgery, comparing intraoperative GIK infusion, insulin bolus regimen and GPL-1 (liraglutide) treatment.

## Methods/Design

### Ethical approval

This study protocol was approved by the medical ethical committee of the Academic Medical Centre in Amsterdam and by the central committee on research involving human subjects (CCMO) acting as competent authority. The study protocol adheres to the Declaration of Helsinki and the guidelines of Good Clinical Practice (GCP). The study is registered at http://www.clinicaltrials.gov # NCT02036372.

### Trial design

The study is a multicentre open-label randomised controlled trial in adult patients with DM type 2, to evaluate the best treatment algorithm to lower glucose in the intraoperative setting, utilizing three parallel study arms. We will compare a glucose-insulin-potassium (GIK) infusion to an insulin bolus regimen and to treatment with the GLP-1 agonist liraglutide. The consort flow diagram of the trial is shown in Figure 1.

**Figure 1 Fig1:**
[figure not shown]
**Consort flow diagram of PILGRIM trial.**

### Eligibility criteria

Patients with DM type 2, treated with oral glucose lowering tablets or a moderate dose of insulin, scheduled for non-cardiac surgery will be eligible for inclusion. This is also in concordance with the population studied in the RABBIT 2 surgery trial [19], showing a reduction in postoperative complications when lowering glucose by 1 mmol l^−1^. Further inclusion and exclusion criteria are listed below. We set a maximum of insulin dose per day, as we do not expect clinical effect from the GLP-1 agonist treatment when patients are treated with a daily dose of insulin >1 IU kg^−1^ bodyweight. Patients with a planned postoperative stay at the intensive care unit (ICU) will be excluded, as the participating ICU’s use a stricter glycaemic target, compared to the wards. Considering the suggested increased risk of pancreatitis when using GLP-1 analogues, patients with a history of acute or chronic pancreatitis are excluded. This point is more extensively addressed in the discussion section.

### Inclusion criteria

Signed informed consentknown diabetes mellitus type 2 for >3 monthsaged 18–75 yearsscheduled for elective non-cardiac surgerydaily insulin dosage of <1 IU kg^−1^ body weight

### Exclusion criteria

Oral corticosteroid useTreatment with long acting GLP-1 agonist or DDP-4 inhibitorPlanned for day-care (ambulatory) surgeryPlanned ICU stay post-operativelyPlanned bowel surgeryHistory of chronic pancreatitis or idiopathic acute pancreatitisImpaired liver function, defined as alanine aminotransferase (ALAT) ≥2.5 times upper normal limitImpaired renal function defined as serum-creatinine ≥133 μmol l^−1^ for males and ≥115 μmol l^−1^ for femalesFemales of child bearing potential who are pregnant, breast-feeding or intend to become pregnant or are not using adequate contraceptive methods (adequate contraceptive measures as required by local law or practice)Known or suspected allergy to trial product(s) or related productsAny condition that the local investigator feels would interfere with trial participation or the evaluation of results

### Study outline

The patients will be recruited during a pre-assessment visit at the anaesthesiology department, where written and oral information will be provided to each patient. Written informed consent will be obtained either at the pre-assessment visit or prior to surgery. For each patient, age, weight, length, relevant medical history and current medication use will be recorded. During the trial, prophylactic dexamethasone treatment for postoperative nausea and vomiting (PONV) is not allowed, as it is unknown to what extent dexamethasone influences glucose in patients with DM. The anaesthetic details will be noted and the grade of nausea and vomiting will be evaluated 1 hour before surgery and 4 hours after surgery using the PONV intensity scale [21] and numeric rating scale (NRS). Thirty days postoperatively, all patients will be called for the assessment of postoperative complications (Tables 1, 2 and 3) and we will review the charts of the patients. Patients will be called at least at three different dates and times to minimize bias due to lost to follow up. All the data will be entered in a digital, good clinical practice (GCP) approved database. During the whole study period, all (serious) adverse events will be recorded and reviewed by the Principal Investigator, according to the GCP guidelines. If it is determined that a medication related serious adverse event presents an unreasonable risk to patients, we will terminate the study or part of the study presenting that risk. The trial will be monitored by an independent monitor.

**Table 1 Tab1:** **Composite endpoint major complications**

Major complications	Definition
Death	30- day mortality of any cause
Re-admission	Unplanned admission within 30 days after discharge
ICU-admission	Unplanned ICU-admission within 30 days after discharge
Re-operation	Unplanned surgical intervention within 30 days after discharge
Deep wound infection	CDC definition [23]
Pneumonia	CDC definition [23]
Sepsis/bacteremia	CDC definition [23]
Myocardial infarction	ECG changes/elevated troponine T and/or CK-MB enzymes
Cerebrovascular event	Diagnosed by CT-scan
Deep venous thrombosis	Diagnosed by Doppler and treatment started
Lung embolus	Diagnosed by spiral CT-scan
Stent thrombosis	Requiring surgical intervention
Bleeding	Requiring intervention or transfusion of RBC’s
Respiratory failure	Requiring intubation/ventilator assistance >24 hours
Renal failure	Requiring dialysis

ICU = intensive care unit, CDC = centre for disease control, CXR = chest X-ray, ECG = electrocardiogram, RBC = red blood cells.

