**Table 3 Tab3:** **Composite endpoint diabetes related complications**

Diabetes related complications	Definition
Hypoglycaemia	For which assistance was required
Diabetic Ketoacidosis	For which admission was required
Seeking medical help	Unplanned appointment with physician or DM nurse
Change in medication	Change in dose or medication stopped within 30 days of surgery
New medication	Additional diabetes medication started within 30 days of surgery

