### Postoperative complications

The occurrence of postoperative complications will be assessed one month postoperatively. This will be determined via chart review and telephone contact. We will use a composite endpoint of postoperative complications derived from the RABBIT 2 surgery trial [19] and DelIT trial [22]. The definition of major and minor complications is shown in Tables 1 and 2. We used the definition of the centre for disease control (CDC) for the various infectious complications [23]. The occurrence of nausea and vomiting during hospital admission will be assessed and scored on the NRS scale. Diabetes related complications are shown in Table 3.

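### Two rows of the major-complications composite start counting at discharge, so they miss index-stay events and, with re-admission, run past the day-30 assessment

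*Protocol article*

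**What the plan says.** Table 1 lists 15 components of the major-complications composite. Three are timed from discharge:

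- ICU-admission: "Unplanned ICU-admission within 30 days after discharge"
- Re-operation: "Unplanned surgical intervention within 30 days after discharge"
- Re-admission: "Unplanned admission within 30 days after discharge"

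Death is given as "30- day mortality of any cause", with no stated start. The other 11 rows carry no time window.

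Two places fix when the outcome is assessed. Study outline: "Thirty days postoperatively, all patients will be called for the assessment of postoperative complications", with a chart review. Postoperative complications: "The occurrence of postoperative complications will be assessed one month postoperatively", followed by "This will be determined via chart review and telephone contact". No later contact is described.

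Table 3, for diabetes-related complications, times its medication rows from surgery, for example "Additional diabetes medication started within 30 days of surgery". The Exclusion criteria rule out day-care surgery and a planned postoperative ICU stay. Outcome measures lists the occurrence of major complications among the secondary outcomes.

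**The concern.** Discharge is the natural starting point for a re-admission. It is not natural for an ICU transfer or a second operation, which can happen while the patient is still in hospital after the index procedure. Because day-care surgery is excluded, every patient has a planned stay during which these two rows are closed. Because a planned ICU stay is excluded, an ICU admission during that stay would ordinarily be just the unplanned event the row is meant to record.

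There is a second problem at the other end. A window that opens at discharge and lasts 30 days cannot be complete at an assessment made 30 days after surgery, unless the patient leaves on the day of the operation.

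What is at stake is the event count in a secondary composite that compares the three arms. Some serious in-hospital events could be recorded as no event, and some late events could be sought in one patient and not in another. If staff chose to count index-stay events despite the wording, they would be doing so case by case in a trial where researchers know the allocation.

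**Working it through.** The plan states no figure on this point, so there is none to reproduce. The check sets the windows side by side and then applies calendar arithmetic.

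**Step 1: what the rows include.** Let surgery be day 0 and discharge day L.

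| Component | Window as written | Index stay (day 0 to L) counted by this row? |
|---|---|---|
| ICU-admission | day L to L + 30 | no |
| Re-operation | day L to L + 30 | no |
| Re-admission | day L to L + 30 | not applicable |
| Death | 30 days, start not stated | not determinable |
| Other 11 rows | none stated | not excluded |

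No other text in the article extends the ICU or re-operation row to the index stay.

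**Step 2: what the other rows catch.** Of the 15 rows, 15 − 3 = 12 have no discharge anchor. A return to theatre on day 2 for bleeding still counts, through the bleeding row. An ICU transfer for sepsis, myocardial infarction or ventilation beyond 24 hours also counts through its own row. A re-operation or ICU transfer for a reason with no row of its own does not count.

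**Step 3: the end of the window.** The window closes on day L + 30 and the assessment is on day 30. Days after the assessment = (L + 30) − 30 = L. Share of the window = L / 30. The article gives no length of stay, so L is an assumption, shown over a range.

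| Assumed L (days) | Window (postoperative days) | Days after the assessment | Share of the 30-day window |
|---|---|---|---|
| 1 | 1 to 31 | 1 | 1/30 = 3% |
| 3 | 3 to 33 | 3 | 3/30 = 10% |
| 5 | 5 to 35 | 5 | 5/30 = 17% |
| 7 | 7 to 37 | 7 | 7/30 = 23% |

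The mismatch exists for every L of at least 1 and affects all three discharge-anchored rows. The percentages are shares of days in those rows. They are not shares of events or of the composite.

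**Step 4: after the change in the fix.** With a window from surgery to day 30, the index stay is counted for ICU admission and re-operation, and the number of days after the assessment falls from L to 0 for all three rows.

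**The case against.** The best defence is that the practical loss is small. Twelve of the 15 rows are open during the index stay, and they cover many of the reasons for which a patient returns to theatre or goes to the ICU. The composite is secondary and the sample size was not set on it. Study treatment ends 4 hours after surgery. The defence stands as a limit on the size of the problem. It does not repair the two rows, whose text is specific and is not corrected elsewhere.

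A reader might infer four stronger points that the article does not support:

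- *All serious in-hospital complications are lost.* They are not. The loss is confined to index-stay ICU admissions and re-operations that no other row captures.
- *The composite mixes a surgery clock for death with a discharge clock for the rest.* The death row gives no start, so this is a guess. The surgery-anchored windows that can be cited are in Table 3, which is a different composite.
- *The last L days cannot be observed.* Chart review is planned as well as the call, and calls may be tried on at least three dates, so some patients may be followed past day 30. The tail is not assured, which is a weaker statement.
- *An arm that shortens stay gains an advantage.* As defined, every patient has the same 30 days after discharge. The observed part varies with L only if ascertainment stops at day 30, and the article gives no reason to expect stay to differ between arms.

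It could also be said that the full protocol may clarify the point. That would answer a missing detail. Here the article states a definition, and that definition conflicts with its own assessment time.

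**Conclusion.** The point holds in a limited form. As written, the ICU-admission and re-operation rows exclude unplanned events during the index stay, and those events enter the composite only through another row. For these two rows and re-admission, the window ends L days after the assessment, which is 3% to 23% of the window for an assumed L of 1 to 7 days, and ascertainment of that part is not assured.

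The first conclusion rests on the literal text alone. The second also rests on reading the stated 30-day or one-month assessment as the end of routine ascertainment. The percentages rest on the assumed length of stay. The number of events affected cannot be derived from the article, and no bias between arms is shown.

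This should be fixed, because a written rule gives a wrong classification and the correction is simple. It does not threaten the primary outcome, which is glucose 1 hour after surgery, or the sample size.

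**What to change.** In Table 1 and the case report form:

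- ICU-admission and re-operation: count unplanned events from the end of surgery through postoperative day 30.
- Re-admission: count unplanned admissions from discharge through postoperative day 30.
- Death: state that the 30 days start at surgery.

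This aligns the rows with the day-30 call and chart review and with the surgery-based timing already used in Table 3.

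The cost is more than a change of wording. The trial started in January 2014 and is open label, so the change needs a dated, documented amendment. The new definition must be applied in the same way to patients already enrolled; the planned chart review is the source for this. One trade-off should be accepted openly: the time at risk for re-admission becomes 30 − L days, for example 30 − 7 = 23 days after a 7-day stay, but every patient then has the same day 0 to 30 for the composite as a whole. No sample-size figure changes.

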**Table 2 Tab2:** **Composite endpoint minor complications**

Minor Complications	Definition
Cystitis or urinary tract infection	CDC definition [23]
Superficial wound infection/wound leakage	CDC definition [23]/leakage of the wound requiring longer duration of hospital stay
Pancreatitis	Clinical diagnosis/Elevated amylase or lipase
Ileus	Lasting more than 72 hours
Delirium	Clinical diagnosis
Length of hospital stay	In days

CDC = centre for disease control.

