### Randomisation

If eligible, patients will be randomised into one of the three study arms. The randomisation will be 1:1:1 for each study arm, with stratification for insulin use. We will use block randomisation with random block sizes, ranging from 3 to 12. The randomisation will be performed with a computer based randomisation application (TENALEA Clinical Trial Data Management System). Patients and investigators are not blinded for the treatment allocation. All patients randomised will be included in the intention to treat analysis.

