### Laboratory measurements

HbA1c, potassium and fasting serum glucose will be determined 1 h prior to surgery. Fasting serum glucose and potassium will be determined 1 hour, 4 hours and on day 1 postoperatively. When the patient has an arterial catheter during the surgical procedure, arterial glucose will be measured.

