## Discussion

Insulin infusion has been a long established regime for the treatment of DM in the perioperative period and is frequently combined with glucose and potassium for safety reasons [5, 25]. Moreover, a continuous infusion of glucose might reduce peripheral insulin resistance [26]. An alternative for the GIK infusion is an intravenous insulin bolus regime. Although no difference was seen in perioperative glucose control in insulin naïve- and insulin-dependent patients, an intravenous bolus regime might be less time consuming than a GIK infusion plus bolus regime [27, 28]. GLP-1 agonists have potential advantages over established DM treatments with insulin during the intraoperative period, due to the low risk of hypoglycaemia. For proper execution of all regimes, perioperative glucose measurements are mandatory.

Since the start of GLP-1 treatment, it has been suggested that the use of GLP-1 agonists is associated with an increased risk of pancreatitis [29]. However, patients with DM type 2 and obesity, regardless of treatment, have an increased risk of developing pancreatitis compared to patients without DM [30]. A recent meta-analysis of 55 randomized controlled trials (n = 33,350) showed no increased risk for pancreatitis in patients using GLP-1 agonists (OR 1.05, 95% CI 0.37 to 2.94) [31]. Also in a large observational trial with over 20,000 new incretin users, no increased risk for pancreatitis was found when compared to patients with DM using sulfonylureas, HR 1.00, 95% CI 0.59 to 1.70 [32]. Although these studies do not completely exclude the possibility of a slightly elevated risk of pancreatitis when using GLP-1 agonists, they are reassuring and an encouragement for more clinical trials using these new substances.

We think that the combination of perioperative use of GLP-1 agonists compared with more established perioperative treatment regimes, makes this a relevant trial on the optimal intraoperative treatment of DM during non-cardiac surgery.

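### The pancreatitis row of Table 2 sets no enzyme threshold and leaves its slash undefined, so in an open-label trial an isolated amylase or lipase elevation can count as an event

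*Protocol article*

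**What the plan says.** The section on postoperative complications refers to Tables 1 and 2 for the definitions of major and minor complications, so these rows are the stated rules.

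- **Pancreatitis (Table 2, minor composite):** "Clinical diagnosis/Elevated amylase or lipase". There is no multiple of the upper normal limit, and no symptom or imaging criterion.
- **Myocardial infarction (Table 1, major composite):** "ECG changes/elevated troponine T and/or CK-MB enzymes". This has the same form and again no threshold.
- **Blinding (Abstract):** "Researchers, care givers and patients will not be blinded for the assigned treatment". The Randomisation section agrees: "Patients and investigators are not blinded for the treatment allocation".
- **Concern about one drug class (Eligibility criteria):** "Considering the suggested increased risk of pancreatitis when using GLP-1 analogues, patients with a history of acute or chronic pancreatitis are excluded". The Discussion adds that "it has been suggested that the use of GLP-1 agonists is associated with an increased risk of pancreatitis". Only the LG arm receives such a drug.
- **Scheduled tests (Laboratory measurements):** "HbA1c, potassium and fasting serum glucose will be determined 1 h prior to surgery"; after surgery, only glucose and potassium are listed. Amylase and lipase do not appear.
- **Ascertainment:** chart review and a telephone call at one month. No arm-concealed assessment is described.
- **Role:** the complication composites are secondary outcomes; the primary outcome is serum glucose one hour after surgery.

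**The concern.** If either side of the slash is enough, a patient with a slightly raised amylase or lipase and no other evidence is coded as having pancreatitis. Because the enzymes are not scheduled, a patient can meet that criterion only if someone orders the test. Those ordering it know the arm, and the protocol has told them which arm carries the suspected risk. More testing in that arm would produce more coded pancreatitis there, even with no true difference.

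At stake is the comparison for a safety event that the protocol itself raises for GLP-1 agonists, and to a lesser degree the minor-complication composite. A small spurious LG excess could be read as support for the very concern that the Discussion tries to put in proportion.

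**Working it through.** **1. How the slash reads.** The tables give evidence both ways.

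- *For alternatives:* in Table 2 a clinician's diagnosis is by itself enough for delirium. Requiring more of the same phrase in the pancreatitis row would be inconsistent. Where Table 1 needs two conditions together, as for deep venous thrombosis (Doppler finding and start of treatment), it writes *and*. The wound row of Table 2 uses a slash between the CDC definition and "leakage of the wound requiring longer duration of hospital stay", either of which qualifies.
- *Against:* the wound row's label also contains a slash, so its two definitions may simply map to two named events. In the pancreatitis row the authors write *or* between the enzymes but a slash before them.

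The either-suffices reading is the more natural one but is not certain. On both readings the size of a qualifying elevation is undefined.

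**2. The figure used as denominator.** The article gives no rate for any complication, so the only figure to reproduce is the arm size.

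- SDs 1.8 and 2.4 (Sample size calculation): √[(1.8² + 2.4²)/2] = √4.5 = 2.121.
- n = 2 × (1.96 + 1.2816)² × 4.5 / 1² = 94.6, so 95 per arm (two-sided 5%, 90% power).
- 10% drop-out: 95 × 1.10 = 104.5, so 105; or 95 / 0.90 = 105.6, so 106. The stated 105 is reproduced.

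The endpoint wording plays no part in this calculation.

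**3. Expected false events, if either side suffices.** With t the proportion tested and f the proportion of tests raised without disease:

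- false events per arm = 105 × t × f
- LG excess over one insulin arm = 105 × f × (t_LG − t_ins)

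Assumptions, none from the documents: t_LG 10%, 30% or 50%; t_ins 2%, 5% or 10%, always below t_LG; f 5%, 10% or 20%.

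- LG arm: from 105 × 0.10 × 0.05 = 0.5 to 105 × 0.50 × 0.20 = 10.5.
- Each insulin arm: from 105 × 0.02 × 0.05 = 0.1 to 105 × 0.10 × 0.20 = 2.1.
- Smallest excess: 105 × 0.05 × (0.10 − 0.05) = 0.3.
- Largest excess: 105 × 0.20 × (0.50 − 0.02) = 10.1.

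If both elements are required, a laboratory value alone adds no events.

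**4. Effect on the minor composite.** Assume a true rate b in both arms, with a proportion a of false events added in LG only. Then p_LG = 1 − (1 − b)(1 − a). The chance of a nominally significant LG excess against one insulin arm is about Φ[(d − 1.96 SE₀)/SE₁], where d = p_LG − b, SE₀ uses the pooled rate and SE₁ the separate rates.

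Example, b = 20% and a = 5%: p_LG = 0.24, d = 0.04, SE₀ = 0.0572, SE₁ = 0.0571, so (0.04 − 0.1121)/0.0571 = −1.26, giving 10.4%.

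| Added false events in LG | b = 10% | b = 20% | b = 30% |
|---|---|---|---|
| 0% | 2.5% | 2.5% | 2.5% |
| 1% | 4.0% | 3.5% | 3.2% |
| 2% | 6.2% | 4.7% | 4.1% |
| 5% | 16.7% | 10.4% | 7.8% |
| 10% | 45.7% | 27.2% | 18.7% |

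The last row is the extreme of step 3 (50% tested × 20% raised). The 2% row corresponds to 10% tested × 20% raised, about two patients.

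**The case against.** The strongest reply is that the article never says one abnormal value is enough. The slash is undefined, and a clinical diagnosis backed by a raised enzyme is a possible meaning under which the problem largely disappears. This stands in part. A reader might infer that the row settles the matter; it does not. The firm statement is that the rule is unclear and that its more natural reading admits isolated elevations.

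Second, differential testing is inferred. No section describes enzyme tests prompted by liraglutide. The Eligibility criteria turn the concern into an exclusion, and the Discussion calls the evidence reassuring (OR 1.05, 95% CI 0.37 to 2.94; HR 1.00, 95% CI 0.59 to 1.70). This stands: the design permits such testing but does not show it.

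Third, the numbers are small under moderate assumptions. Two percent added events moves the chance of a nominally significant excess only from 2.5% to 4.7% at a 20% base rate. This stands too.

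Fourth, a journal article shortens definitions, and a cut-off may sit in the full protocol. That would excuse a missing detail. It does not remove the ambiguity in a row that the article presents as the definition.

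Finally, a reader might extend the one-arm argument to myocardial infarction because its row is built the same way. The documents name no cardiac concern for any arm, so that step has no support. Nor is pancreatitis the only issue particular to LG: that arm alone has a rule tying its second dose to nausea.

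**Conclusion.** The point holds in limited form. The pancreatitis row has no enzyme threshold, and on its more natural reading an isolated elevation of any size enters the minor composite. With open allocation, unscheduled enzyme tests and a stated concern about one drug class, a spurious LG excess is possible.

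Its size cannot be known from the documents. Under the assumed rates it runs from almost none to about 10 events per 105 patients, and the upper end needs half the LG arm to be tested and a fifth of those tests to be raised without disease. The result rests on the either-suffices reading and on more frequent testing in LG, neither of which the article establishes.

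The effect is confined to a component of a secondary composite; the primary glucose comparison and the sample size are untouched. For myocardial infarction the finding is only that the wording is unclear. The correction is worth making because it is cheap, not because the trial's main conclusion is at risk.

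**What to change.** **Table 2, pancreatitis.** State that an amylase or lipase elevation alone does not qualify. Require a clinical diagnosis supported either by an enzyme elevation above a prespecified multiple of the upper normal limit or by imaging. The documents give no basis for a particular multiple, so the trial team should choose it and record it before the arms are compared. Report isolated elevations by arm, outside the composite.

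**Coding.** Apply the rule identically in all arms during the chart review already planned, with the arm concealed from the coder where existing staff allow. The definition does not make test ordering uniform, and clinical diagnoses are still made by unblinded staff. Concealed coding and the separate count of isolated elevations help to make any imbalance visible.

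**Table 1, myocardial infarction.** Say whether ECG changes and raised markers are both required.

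**Cost.** Two rows of wording and slightly fewer counted events. No new tests, visits or staff are needed.
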